### 18.3 DETERMINATION OF THE NUMBER OF SUBJECTS

In paragraph 1 of this protocol, we specify the total number of patients to 16. The higher number is a way to keep abreast of any shortfall, but the analysis are so costly that the intention is to cancel the recruitment when we reached the 10 evaluable patients.

With 10 evaluable patients there is a power of 80% to detect a difference of effect size 1 with a 2-sided t-test and a significance level of 5%. The absolute albumin synthesis rate has been measured at  $131 \pm 21$  mg/kg/day in healthy subjects (control group) where intra-individual standard deviation for repeated measurement after 2.5 hours was 11 mg/kg/day [Barle 2002], which can be perceived as the uncertainty of the method in this specific and very controlled situation. With repeated measurements on ICU patients with 5-day intervals corresponding values were  $233 \pm 67$  and 70 mg/kg/day [Barle 2001a]. There is reason to believe that in this case we will fall between these figures. If the variation of the change is 30 mg/kg/day a difference in the absolute synthesis rate of 30 mg/kg/d can be detected with 80% power. We believe this to be a clinically relevant change.

Some patients can be expected to have increased capillary leakage (TER) in the basal measurement (before surgery) due to hypertension, diabetes and malignancy, but this is less of a problem when the patients serve as their own controls.

Ten patients, give an 80% power to detect a correlation between, for example, capillary leak and synthesis rate if  $r$  is greater than 0.71 ( $r^2 \geq 0.5$ ) with a two-sided test and a significance level of 5%.

We have not found any published measurements of neither synthesis rate or capillary leakage of albumin in this patient group. Any assumption regarding the distribution and change in albumin kinetic parameters thus becomes unsure. There is a risk that this pilot study proves to be a bit too weak in power, but it is very resource intensive measurements, and if so we can submit an amendment to expand the investigation. The large number of correlations mentioned above must be seen against the background that this is an exploratory pilot study of physiological changes in scheduled surgery. There is thus an intention that the study is mainly hypothesis generating.

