## 9 DESIGN

### 9.1 DESIGN OVERVIEW

The study is a prospective, open, explorative pilot study of surgical patients scheduled for major abdominal surgery, pancreatic resection. A low dose of radioactive iodine (SERALB-125), will be injected intravenously on two occasions to study the albumin kinetics. At the same occasion, a flooding dose of deuterium labeled phenylalanine will be given. The actual study time is estimated to be about four hours spread over two days. The kinetics will be monitored for 90 minutes after the injection has been given. The first dose will be injected on the day of surgery, the second about two days after surgery. All other treatment will be given according to routine clinical practice. Recruitment will continue until 10 evaluable patients have completed all measurements. The staff who perform the laboratory analyzes will be "blinded".

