## 18.2 STATISTICAL ANALYSIS

There is evidence that the rate of synthesis of albumin, measured as fractional or absolute synthesis rate, increase in states of general inflammation that occurs after this kind of surgery. Furthermore, albumin capillary leakage increases as measured by the fraction of albumin in the blood and the total outflow of albumin from the blood. The endpoint is the change in these four parameters. To take the step from fractions to absolute values requires an assessment of plasma volume, P-albumin and body weight. All data will be presented as mean with standard deviation (SD) or as median and range of data if not normally distributed. The changes in the variables will be tested with two-sided paired t-test alternative Wilcoxon's test with a significance level of 0.05.

Furthermore, the mutual correlations between the four kinetic albumin parameters as well as with P-albumin will be calculated and presented with correlation coefficients. That changes in capillary leakage and synthesis rate could correlate is reasonable, but not previously described.

Correlation between the above kinetic albumin variables and degree of SIRS (HR, LPK, temperature, respiratory rate) including CRP will be explored. It is reasonable to believe that the degree of inflammation affects the change of albumin variables. Influence of pre-operative weight loss on albumin preoperative kinetic variables will also be analyzed, because weight loss could be a factor that already pre-operatively affects albumin kinetic variables. Correlations will be reported as Pearson correlation coefficient  $r$  or Spearman's rank correlation  $r_s$  depending on the data's nature.

Demographic preoperative data such as age, height, weight, BMI, gender, some routine lab, preoperative weight loss, duration of pancreatic disease, diagnoses, current medications, completing

chemotherapy and ASA class will be presented as numbers, averages and standard deviation, or median range depending on the data's nature. Likewise per- and postoperative demographics such as surgery haemorrhage, supplied anesthetics including epidural anesthesia (doses, number), given fluid infusions including blood products (ml), surgical procedure, post-operative medical or surgical complications, postoperative drug delivery, including the epidural, and laboratory test according to routine will be reported.

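### The 80% power stated for a correlation of 0.71 with ten patients does not fit the planned analysis: for two measured variables it is about 70%, and 80% needs r of about 0.76

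*Protocol*

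**What the plan says.** Section 18.3 gives two power statements for ten evaluable patients. The first concerns a paired difference of effect size 1. The second is the one at issue: "Ten patients, give an 80% power to detect a correlation between, for example, capillary leak and synthesis rate if" r "is greater than 0.71", glossed as r squared of at least 0.5, with a two-sided test at the 5% level. No formula or software is named.

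The number ten agrees with section 9.1: "Recruitment will continue until 10 evaluable patients have completed all measurements".

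Section 18.2 describes the analysis this power is meant to support: "the mutual correlations between the four kinetic albumin parameters as well as with P-albumin will be calculated and presented with correlation coefficients". It continues: "Correlations will be reported as Pearson correlation coefficient" r, or Spearman's rank coefficient, depending on the data. Section 7.2 lists the correlation of kinetic parameters with each other as a secondary question.

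Section 18.3 also concedes that the pilot may turn out underpowered, allows for an amendment to enlarge it, and closes the discussion of the many correlations with: "There is thus an intention that the study is mainly hypothesis generating".

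**The concern.** Capillary leak and synthesis rate are both outcomes measured in the patient. Neither is set by design and neither is a two-group indicator. The power of a test of their correlation has to allow for sampling variation in both, and that lowers it noticeably when n is only ten. A figure that leaves this out is too favourable.

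What is at stake is how a non-significant result is read. Section 18.2 presents a link between synthesis and leakage as plausible but new, and section 18.3 uses that pair as its example. A reader who trusts the stated power would expect a true correlation of 0.71 to be missed in two such studies out of ten, when the expected number is about three. Section 18.3 also keeps open an amendment to expand the study if power proves too low, and that decision should rest on a correct figure.

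**Working it through.** **Inputs, all from sections 18.2 and 18.3:** n = 10; r = 0.71 (or r = 0.7071 if r squared is exactly 0.5); two-sided 5%; Pearson coefficient between two measured variables.

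**Critical value.** With 8 degrees of freedom the two-sided 5% point of t is 2.306. The critical correlation is 2.306 / √(2.306² + 8) = 0.632.

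**Step 1: reproduce the stated 80%.** Treat one variable as a fixed predictor. The test statistic is then noncentral t on 8 df with δ = √n · r / √(1 − r²).
- r = 0.71: δ = 3.162 × 0.71 / √(1 − 0.5041) = 3.188; two-sided power 79.7%.
- r squared = 0.5: δ = √10 = 3.162; power 79.1%.
- Power is 80% at r = 0.711.

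This matches the protocol's figure almost exactly.

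**Step 2: the planned analysis, both variables random.** Under bivariate normality the sum of squares of the predictor is itself random, a chi-square on n − 1 = 9 df in units of its variance. The noncentrality becomes δ = r / √(1 − r²) × √(χ² on 9 df), and the power is averaged over that distribution.
- r = 0.71: power **69.9%** (simulation 70.0%).
- r squared = 0.5: power 69.4%.
- r needed for 80% power: **0.761**, so r squared = 0.761² = 0.58.

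The gap has two parts. Replacing n = 10 by n − 1 = 9 in the fixed-predictor formula lowers the power from 79.7% to 75.5%. Averaging over the spread of the chi-square takes it to 69.9%.

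**Step 3: cross-check with Fisher's z.** atanh(0.71) = 0.887; 0.887 × √7 = 2.347; 2.347 − 1.960 = 0.387; power 65.1%. With a bias correction it is 68.9%, and with the t critical value 68.5%. The r needed for 80% is 0.785 by plain Fisher z and 0.770 with the t critical value. These approximations are slightly more pessimistic than the exact result, and none comes near 80% at r = 0.71.

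**Step 4: other routes to 80%.** An exact one-sided 5% test gives 80.8% at r = 0.71. The protocol specifies a two-sided test, so this route is excluded.

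**Step 5: Spearman.** The protocol gives no distribution, so these figures assume bivariate normal data and come from simulation.

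| Reading of 0.71 | Exact critical value (0.648) | t approximation |
|---|---|---|
| Pearson, r squared = 0.5 | 57.0% | 59.1% |
| Pearson r = 0.71 | 57.8% | 59.9% |
| Population Spearman = 0.71 | 60.9% | 63.0% |

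The range is about 57% to 63%.

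**Step 6: the other power statement.** Paired t-test, effect size 1, n = 10, two-sided 5%: power 80.3%. That statement is confirmed.

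**The case against.** The strongest reply is that the 80% follows from the protocol's own inputs through a standard noncentral-t calculation, so nothing was miscalculated. That stands as far as it goes. A reader might infer an arithmetic error, but the documents do not support that reading: the number is reproducible, and since no method is named, its origin can only be inferred. The reply does not rescue the sentence, because the model that yields 80% does not describe two measured kinetic parameters.

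A second reply is that the question is secondary, that nothing shows this sentence set the sample size (section 18.3 ties stopping at ten to cost and gives the paired-t power first), and that the same section warns of low power and calls the work hypothesis generating. This stands and limits the importance of the point. It does not correct the figure: the warning is about unknown distributions and effect sizes, whereas the power is overstated at the very r the section specifies. For the same reason, a reader who inferred that the trial is underpowered for its primary question would be going beyond the documents.

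A third reply concerns Spearman. It is tempting to say that power falls to 57% and leave it there. The protocol's sentence is about r and r squared and makes no claim for ranks. The 57% assumes normal data, the case in which Pearson would normally be chosen. For non-normal data the power depends on a distribution that the protocol does not give. Spearman belongs in the correction only as a range with its assumption stated.

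**Conclusion.** The point holds as a mismatch between the power model and the planned analysis. For a two-sided 5% Pearson test of two measured variables with ten patients, power at r = 0.71 is about 70% rather than 80%, and the correlation detectable with 80% power is about 0.76 (r squared about 0.58) rather than 0.71 (r squared 0.5). The result rests on bivariate normality. The Fisher approximations, at 65% to 69%, point the same way.

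The weight is minor to moderate. The correlations are secondary and exploratory, the paired-t statement behind the primary question is sound, and no test or design feature has to change. The sentence should still be corrected, because it is an unqualified numerical claim that will guide how a null correlation is read.

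**What to change.** Replace the correlation sentence in section 18.3 with wording such as:

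> With ten patients, power is about 70% for a Pearson correlation of r = 0.71 (two-sided, 5%, both variables measured and jointly normal). A power of 80% requires r of about 0.76 (r squared about 0.58). Power is lower if Spearman's coefficient is used on approximately normal data (about 57–63%).

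If the sponsor used a different calculation, its method should be named beside the figure. The cost is one sentence and a less favourable number. The sample size, the planned tests and the primary power statement stay as they are.

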## 19 ACCESS TO SOURCE DATA

The primary investigator is responsible that there is a confidentiality agreement between the monitor or any other independent reviewer (*i.e.* auditor) given permission to verify the data in the patient record and the patient record responsible party at Dept of Anesthesiology and Intensive Care. This requires the patient's written consent.

## 20 QUALITY CHECK

### 20.1 MONITORING

The investigator with staff must set aside time for monitoring, audits, and regulatory inspections. The sponsor is responsible for monitoring by independent monitor with knowledge of GCP, to ensure that the study is performed in accordance with GCP, the study protocol and regulatory requirements. The sponsor has contracted Karolinska Trial Alliance for monitoring of this study.

## **21 ETHICS**

### **21.1 ETHICAL REVIEW BOARD**

The investigator is responsible for the application for approval from the Ethics Review Board. Sponsor's responsibility is to send a copy of the approval to the Swedish MPA.

### **21.2 ETHICAL CONDUCT OF THE STUDY**

The study will be conducted according to the study protocol, GCP, regulatory requirements and the Helsinki Declaration.

## **22 DATA MANAGEMENT AND ARCHIVE**

### **22.1 CASE REPORT FORMS**

Data collected in the study and registered in the CRF will be transferred to a database that the sponsor is responsible of.

Data collected in the study will be recorded in Case Report Forms (CRF) in which the patient is only identified with a code number and initials. The code key kept by the investigator in such a way that unauthorized persons cannot take part of it. Anonymous and coded copies of medical records such as anesthesia records, monitoring sheet for post-operative care, journal text (Take Care) and laboratory lists (Take Care) will also be included in the CRF.

### **22.2 ARCHIVE**

Study documents will be filed at least 10 years after the study report is submitted to the Swedish MPA. The documents should be archived in a legible condition for eventual future audit or inspection by authorities.

## **23 FINANCIAL SUPPORT AND INSURANCE**

The study is funded by research grants. The patients are insured through medical insurance and patient injury insurance.

## **24 PUBLICATION OF RESULTS**

The intention is to publish the results in a scientific journal.

## 27 ATTACHMENTS

### 27.1 Flow chart

|                                             |  | DAY - 14 (DAY -28 TO -2) | DAY -1 (DAY -3 TO -1) | DAY 0 | DAY 2 (DAY 1 TO DAY 4) | DAY 5 (DAY 4 TO DAY 7) |  |  |  |  |  |  |  |  |
|---------------------------------------------|--|--------------------------|-----------------------|-------|------------------------|------------------------|--|--|--|--|--|--|--|--|
| Investigator visit                          |  | X                        | X                     | X     | X                      | X                      |  |  |  |  |  |  |  |  |
| Blood sampling ROUTINE                      |  | X                        |                       | X     | X                      | X                      |  |  |  |  |  |  |  |  |
| Oral study information                      |  | X                        | X                     |       |                        |                        |  |  |  |  |  |  |  |  |
| Written patient information                 |  | X                        |                       |       |                        |                        |  |  |  |  |  |  |  |  |
| Written consent                             |  | (X)                      | X                     |       |                        |                        |  |  |  |  |  |  |  |  |
| Inclusion/exclusion criteria                |  |                          | X                     |       |                        |                        |  |  |  |  |  |  |  |  |
| Demographic data                            |  |                          | X                     | X     | X                      | X                      |  |  |  |  |  |  |  |  |
| Diseaseses                                  |  |                          | X                     |       | X                      | X                      |  |  |  |  |  |  |  |  |
| Ongoing medication                          |  |                          | X                     |       | X                      | X                      |  |  |  |  |  |  |  |  |
| Blood sampling: P-Albumin, P-CRP            |  |                          |                       | X     | X                      |                        |  |  |  |  |  |  |  |  |
| Blood sampling: B-LPK                       |  |                          |                       | X     |                        |                        |  |  |  |  |  |  |  |  |
| Urine-HCG (women)                           |  |                          | X                     |       |                        |                        |  |  |  |  |  |  |  |  |
| Radiolabeled iodine injection, dose #1      |  |                          |                       | X     |                        |                        |  |  |  |  |  |  |  |  |
| Radiolabeled iodine injection, dose #2      |  |                          |                       |       | X                      |                        |  |  |  |  |  |  |  |  |
| Isotopelabeled injection of d5-phenylalanin |  |                          |                       | X     | X                      |                        |  |  |  |  |  |  |  |  |
| Vital parameters (BP, AF, pulse, temp)      |  |                          | X                     | X     | X                      | X                      |  |  |  |  |  |  |  |  |
| Adverse events                              |  |                          |                       | X     | X                      |                        |  |  |  |  |  |  |  |  |
|                                             |  |                          |                       |       |                        |                        |  |  |  |  |  |  |  |  |
|                                             |  |                          |                       |       |                        |                        |  |  |  |  |  |  |  |  |
